**7. Does the patient have diabetes that requires treatment? (DM)**

- Yes
- No

*Criteria: Diabetes includes all patients with diabetes treated with insulin or oral hypoglycaemic, but not diet alone. Diabetes during treatment is not counted.*

**7a. Does the patient have end organ damage from diabetes? (DM ENDORGAN)**

- Yes
- No

*Criteria: This includes patients with retinopathy, neuropathy, or nephropathy attributable to diabetes.*

**8. Does the patient have moderate or severe renal disease? (RENAL)**

- Yes
- No

*Criteria: Moderate renal insufficiency includes patients with a serum creatinine >3mg/dl. Severe renal disease includes patients on dialysis, those who had a transplant, and those with uremia.*

**9. Does the patient have a chronic liver disease (MILDLIVER)**

- Yes
- No

*Criteria: Mild liver disease consists of chronic hepatitis (B or C) or cirrhosis without portal hypertension*

**9a. Does the patient have moderate to severe liver disease? (SEVERELIVER)**

- Yes
- No

*Criteria: Moderate liver disease consists of cirrhosis with portal hypertension but without bleeding. Severe liver disease consists of patients with ascites, chronic jaundice, portal hypertensions or a history of variceal bleeding or those who have had liver transplant.*

**10. Has the patient had gastric or peptic ulcers? (ULCERS)**

- Yes
- No

*Criteria: Peptic ulcer disease includes patient who have required treatment for ulcer disease, including those who have bled from ulcers.*

**11. Has the patient had cancer (other than basal cell skin cancer)? (CANCER)**

- Yes
- No

If yes, which:

- - Lymphoma?
  - Leukaemia?
  - Solid tumor (which?) ___________________

*Criteria: Lymphoma includes patients with Hedgkins, lymphosarcoma, Waldenstrom’s macroglobulinaemia, myeloma, and other lymphomas. Leukaemia includes patients with acute and chronic myelogenous leukemia, acute and chronic lymphocytic leukaemia, and polycythaemia vera. Solid tumour consists of patients with solid tumours without documented metastases, including breast, colon, lung, prostate, and a variety of other tumours.*

**11a. Has the patient had a metastatic solid tumour? (METASTASES)**

- Breast □ Lung
- Colon □ Prostate
- Melanoma
- Other _______________________

*Criteria: Metastatic cancer includes patients with metastatic solid tumours, including breast, lung, colon and other tumours.*

**12. Does the patient have Alzheimer’s, dementia from any aetiology or any serious cognitive impairment? (DEMENTIA)**

- Yes
- No

*Criteria: Dementia includes patients with moderate to severe chronic cognitive deficit resulting in impaired function from any cause.*

**13. Does the patient have any rheumatic or connective tissue disease? (RHEUMATIC)**

- Yes
- No

*Criteria: Rheumatologic disease includes patients with systemic lupus erythematous, polymyositis, mixed connective tissue disease, rheumatoid arthritis, polymyositis, polymyalgia rheumatica, vasculitis, sarcoidosis, Sjogrens syndrome or any other systemic vasculitis.*

**14. Does the patient have HIV or AIDS? (HIV)**

- Yes
- No

*Criteria: Acquired immune deficiency syndrome includes patients with definite or probably AIDS i.e. AIDS related complex, and those who are HIV positive and asymptomatic.*

**15. Does the patient have hypertension? (HBP)**

- Yes
- No

*Criteria: Hypertension includes patients who have systolic pressures >140mmHg and/or diastolic pressures >90mmHg if without diabetes or renal disease, as well as controlled hypertensives; or patients with diabetes or renal disease who have systolic pressures >140mmHg or diastolic pressures >80mmHg.*

**16. Has the patient had decubitus ulcers, peripheral skin ulcers or repeated episodes of cellulitis?**

- Yes
- No

*Criteria: Partial thickness loss of skin over legs or back with open ulcers or two or more episodes of cellulitis requiring treatment with antibiotics, regardless of aetiology.*

**17. Does the patient have depression?**

- Yes
- No

*Criteria: Patients who are currently receiving treatment for depression, whether pharmacologic or psychotherapy, or cognitive behavioural therapy, or notes indicating that the patient has probably or definite depression.*

**18. Is the patient on warfarin or Coumadin?**

- Yes
- No

*Comments: ………………………………………………………………………………………………………………………………………………………..*

**…………………………………………………………………………………………………………………………………………………………………………**

## Appendix U – Diuretic Titration Guidelines for Trial Nurses

*This guideline has been developed to assist the ALFIE Nurses to provide timely diuretic titration to patients on these medications. As experienced RNs in the field of Gastroenterology and Hepatology, the ALFIE nurses have received training in diuretic titration during the Investigator Meetings in November 2017 and August 2018. Nurses are encouraged to check with a medical officer if in doubt.*

| Medicine Name: Frusemide (Furosemide) and Spironolactone (Adult) | |
| --- | --- |
| **Formulation:** | Frusemide (Furosemide): 20 mg tablet and 40 mg tablet  Spironolactone: 25mg tablet and 100mg tablet |
| **Specific Condition** | Non tense ascites secondary to advanced liver disease. |
| **Purpose and scope:** | Facilitate timely titration of diuretic treatment of non-tense ascites associated with liver failure, for adult patients enrolled in the ALFIE trial |
| **Limitations:** | Only applies to patients enrolled in the ALFIE trial |
| **Indications for use:** | Non-tense ascites associated with chronic liver disease:   - Patients must be able to monitor weight daily, either alone or with carer input. - Patients and/or carers must be able to understand and implement titration instructions. |
| **Contra-indications:** | - Patients with a known barrier to compliance. - Patients unable to be weighed daily. - Patients/carers unable to understand and implement titration instructions. - Patients with renal impairment who require a Medical Officers input regarding diuretic titration. - *Patients with stable chronic renal impairment may have their diuretics managed by the ALFIE nurse as per this guideline if instructed to do so by the patient’s attending Hepatologist.* - Patients with overt hepatic encephalopathy. |
| **Dose** | - This guideline covers patients who are currently prescribed frusemide (furosemide) and spironolactone by a medical officer for the management of non-tense ascites associated with chronic liver disease. - Doses of spironolactone and frusemide (furosemide) can be titrated up in increments of a half or full dose. - Usually both diuretics are titrated up together but at times dysfunction in electrolytes (Sodium or potassium) may necessitate titration of only one diuretic. - Doses must not exceed a maximum of frusemide (furosemide) 160mg daily or spironolactone 400mg daily. |
| **Frequency:** | ALFIE trial nurses may instruct the patient to increase their dose of frusemide (furosemide) or spironolactone no more than every 5 days (following receipt of electrolyte test results). |
| **Procedure for administration:** | Patients/carers will monitor weight daily and those failing to show adequate weight loss over a five day period and with normal kidney function and electrolytes will be directed by the ALFIE trial nurse to increase their dose of diuretics. |
| **Management of Complications:** | Complications of diuretics:  **Renal failure:** refer to treating medical officer  **Hepatic encephalopathy:** refer to treating medical officer  **Electrolyte disturbances:**  **Hypokalaemia:** reduce if K+ <hold frusemide (furosemide) if serum potassium <3 mmol/L and recheck bloods within 72hrs.  **Hyperkalaemia:** reduce Spironolactone if serum potassium >5.6 mmol/L. Hold spironolactone if serum potassium >6.0 mmol/L. Recheck bloods within 72hrs  **Hyponatraemia:** Reduced diuretics if sodium <130mmol/L. Hold diuretics if sodium < 125 mmol/L. Recheck bloods within 72hrs  **Muscle cramps:** Check electrolytes. If severe, may require discontinuation; Discuss with Medical Officer.  Complications are to be managed by the ALFIE trial nurse and/or treating Medical Officer depending on the severity. |
| **Monitoring requirements:** | - Diuretic titrations up in dose should be followed by a blood test in 5 days and electrolyte imbalance managed with consideration of concomitant therapy (conducted by either the ALFIE trial nurse and/or treating Medical Officer). - Diuretic titrations down in response to kidney or electrolyte dysfunction should be monitored closely with blood tests. |
| **Documentation:** | Any dose changes are to be documented in the patient’s outpatient medical record/EPAS and the GP informed. |

| REFERENCES | |
| --- | --- |

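### The nurse diuretic guideline leaves its hypokalaemia reduce step unfinished, and its rows on dose increases do not say which one governs

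*Protocol*

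**What the plan says.** Appendix U of the protocol (Diuretic Titration Guidelines for Trial Nurses) applies to trial patients with non-tense ascites who are already prescribed both drugs.

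**Management of Complications.** Three electrolyte disturbances are covered:
- For low potassium, the line reads "reduce if K+ <hold frusemide (furosemide) if serum potassium <3 mmol/L and recheck bloods within 72hrs".
- For high potassium, the nurse finds two complete steps: "reduce Spironolactone if serum potassium >5.6 mmol/L. Hold spironolactone if serum potassium >6.0 mmol/L".
- For low sodium, there are again two complete steps: "Reduced diuretics if sodium <130mmol/L. Hold diuretics if sodium < 125 mmol/L".

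**Dose increases.** Four rows bear on when a nurse may direct an increase:
- Procedure for administration: patients without adequate weight loss over five days and "with normal kidney function and electrolytes will be directed by the ALFIE trial nurse to increase their dose of diuretics".
- Dose: the two drugs usually go up together, but "at times dysfunction in electrolytes (Sodium or potassium) may necessitate titration of only one diuretic".
- Frequency: increases come at most every five days, once electrolyte results are in. The row does not say what those results must show.
- Contra-indications: "Patients with stable chronic renal impairment may have their diuretics managed by the ALFIE nurse as per this guideline", provided the attending hepatologist has so instructed.

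**Fallbacks.** The introduction says the nurses were trained in diuretic titration and advises them to ask a doctor when unsure. The complications row shares management between nurse and doctor according to severity. The monitoring row calls for a blood test five days after an increase, with any electrolyte imbalance handled by the nurse, the doctor or both.

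**The concern.** This is an operative instruction that nurses act on, and Appendix U itself lists renal failure, encephalopathy and electrolyte disturbance as complications of the drugs. A comparator with nothing after it cannot be followed. A nurse who sees potassium falling, but not yet at the hold level, can tell that some reduction was intended but not when it starts or which drug it concerns.

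The rows on increases raise a second question. Suppose weight loss is inadequate and sodium or potassium is mildly abnormal. A nurse who reads the Dose row may think one drug can go up. A nurse who reads the Procedure row finds no direction to increase. The trial runs at four sites, and under Training the protocol aims to standardise nursing practice. Rows that can be read differently work against that aim and leave a safety instruction to individual interpretation.

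**Working it through.** No figure in the plan needs reproducing. The check is a comparison of the rows of Appendix U.

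**Step 1: electrolyte thresholds.**

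| Disturbance | Reduce step | Hold step |
|---|---|---|
| Hypokalaemia | comparator only; no value, unit or drug | frusemide, potassium <3 mmol/L |
| Hyperkalaemia | spironolactone, potassium >5.6 mmol/L | spironolactone, potassium >6.0 mmol/L |
| Hyponatraemia | diuretics, sodium <130 mmol/L | diuretics, sodium <125 mmol/L |

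Thresholds implied: 3 disturbances × 2 steps = 6. Thresholds present: 1 + 2 + 2 = 5. Missing: 6 − 5 = 1, the hypokalaemia reduce step. The affected range starts at 3 mmol/L, where "hold frusemide (furosemide) if serum potassium <3 mmol/L" stops applying. Its upper end cannot be stated, because that is the missing number.

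**Step 2: could the gap come from reading the PDF?** No redaction is marked at this place, and every other comparator in the same cell kept its value. A reading loss cannot be excluded from the text alone, but nothing points to one. The signed copy would settle it.

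**Step 3: rows on dose increases, for a patient without adequate weight loss.**

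| Blood results | Procedure row | Other rows | Aligned? |
|---|---|---|---|
| Kidney function and electrolytes normal | increase directed | Dose: usually both drugs; Frequency: results received | yes |
| Kidney function normal, sodium or potassium abnormal | condition not met; row is silent | Dose: foresees raising one drug; Frequency: asks only for results | not stated which governs |
| Stable chronic renal impairment, hepatologist has instructed, electrolytes normal | condition not met; row is silent | Contra-indications: guideline applies | exception not carried across |

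**Step 4: how the two problems meet.** For low potassium at or above 3 mmol/L, the Dose row foresees adjusting a single drug upward, while the unfinished line points to a reduction at some unstated level. Without that level, a nurse cannot tell from the page where one instruction gives way to the other.

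**The case against.** Several points count against a stronger reading.

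- **A reader might infer that one row permits an increase and another forbids it.** The Procedure row does not say this. It is a positive direction for the standard case and contains no prohibition. The Dose bullet can be read as qualifying it: both drugs when results are normal, one drug for some abnormalities. That reconciliation is reasonable, but the reader has to supply it.
- **The renal bullet is an explicit exception.** It depends on a hepatologist's instruction for that patient, which naturally qualifies a general rule, and management also covers reductions, holds and monitoring. This is the weakest part of the point. What remains is that the Procedure row does not carry the exception over.
- **A reader might infer that nothing applies to low potassium above the hold level.** That goes too far. The Procedure row gives no direction to increase when electrolytes are abnormal, and the monitoring, severity and ask-a-doctor clauses still apply. None of them supplies the missing value or drug.
- **A reader might take Appendix U to be the only drug rule that nurses apply themselves.** The Intervention and Implementation section mentions protocols for all major complications, and these are not reproduced, so this cannot be established.
- **A reader might count the whole intervention arm as exposed.** Appendix U limits itself to non-tense ascites, patients able to weigh themselves daily, no known barrier to compliance and no overt encephalopathy, and it excludes renal impairment that needs a doctor's input. The documents do not give the number who qualify.

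**Conclusion.** The hypokalaemia line is wrong as written. One of six implied thresholds is absent, together with the drug it concerns, and the fallbacks soften this without filling it. This is a drafting error in a safety instruction, not a choice of design. The conclusion assumes that the supplied text matches the signed page.

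The rows on dose increases are unaligned rather than plainly contradictory. They agree when all results are normal, and they leave open which governs when electrolytes are abnormal or the renal exception is in use.

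The documents do not support the broader inference that the guideline as a whole cannot be applied safely. The potassium hold step, the other two electrolyte lines, the dose maxima and the recheck interval are all complete. Differences in practice between sites are a plausible consequence but have not been shown. The sample size, primary endpoint and primary analysis are not touched.

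**What to change.** The sponsor should:

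1. Compare the hypokalaemia line with the signed copy and with the standing medication order that Appendix U names as its basis. That order is not among the documents, so it may or may not contain the missing value.
2. Complete the line with its threshold and the drug concerned, under the responsibility of the hepatology lead.
3. Reconcile the Dose, Frequency, Procedure and Contra-indications rows so that the page says which governs when electrolytes are abnormal, and how the exception for stable chronic renal impairment applies to increases.
4. Reissue the page to all four sites.

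This review proposes no threshold, dose or clinical rule. The cost is a one-page correction with a notice to the sites and the ethics committee. It needs no extra visits, tests or staff.

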## Appendix V – ALFIE Interview Questions for Patients

Introduction

Hi, I’m XX. Thank you for your time today. I am not a member of the ALFIE trial but have been asked to assist the research team with conducting these phone interviews. The aim of this interview is to find out about your experience being part of the ALFIE trial.

Questions

1. Tell me about your experience of having your liver disease managed at <your hospital>.
2. Was anyone involved in your care besides doctors?
3. Did you have a special liver nurse in charge of your care?
4. If yes, could you tell us about your experience receiving care from this liver nurse?
5. Did you feel supported during your treatment?
6. Did you receive any education about your liver disease?
7. Did you learn about self-management for the complications of your liver disease?
8. Do you feel confident about receiving appropriate care for your liver disease?
9. What were some of the good things about the care you received for your liver disease?
10. Do you have any complaints about the care received?
11. Is there anything that would have made the care you received for your liver disease any better?
12. Do you have any other feedback about the care you received by the liver department at <your hospital>?

## Appendix W – ALFIE Interview Questions for Staff

Introduction

Hi, I’m XX. Thank you for your time today. I am not a member of the ALFIE trial but have been asked to assist the research team with conducting these phone interviews. The aim of this interview is to find out about your experience being part of the ALFIE trial.

Questions

1. Do you feel that the case management provided has helped the patients in the ALFIE intervention arm compared to standard of care?
2. What were the strengths/benefits of the intervention (case management)?
3. What were the weaknesses of the intervention (case management)?
4. What are the key issues that need to be discussed by the nurses in providing case management?
5. *(For Nurses only)*:
6. Did you feel confident to provide the intervention (case management)?
7. Were you adequately supported with the information provided (such as study protocols and information folders) to perform the intervention?
8. Did you have to be upskilled to provide this role?
9. Describe the learning opportunities given to you to enable you to fulfill this role.
10. Would you like to continue in this role after the trial ends? Why?
11. Would you like to learn more about caring for patients with cirrhosis of the liver?
12. What were the problems encountered in providing the intervention and how were they managed?
13. How can this model of care be improved further?
14. Do you have any other feedback about this model of care?
15. Would you like to see the role implemented at <your hospital> going forward?

Yes/No, please elaborate.
